#### Clinical function assessment and electrophysiological assessment

Clinical function assessment and electrophysiological measurement will be performed at T0, T1, and T2 in Huashan Hospital, Fudan University. The level of motor function will be assessed based on the Brunnstrom stage. Manual muscle test (MMT) and modified Ashworth scale (MAS) will be used to assess muscle strength and muscle tone of the limbs, respectively, whereas the national Institutes of Health Stroke Scale (NIHSS) will be used to assess the severity of neurological deficits in stroke. In addition, Fugl-Meyer Upper Limb Motor Function Rating Scale (FM-UL), Action Research Arm Test Scale (ARAT) and Wolf Motor Function Test Scale (WMFT) will be used to assess the motor function of the affected arm and hand. Activities of daily Living (ADL) will be evaluated using the Modified Barthel Index (MBI).

For electrophysiological evaluation, single-pulse TMS (YRD CCY-4, Yi Ruide Company, Wuhan, China) will be used to assess bilateral hemispherical MEP using a 8-figured coil with an external wing of 7 cm. We will first determine the optimal stimulus point, the location on the scalp with the largest and most consistent MEP in the contralateral Abductor Pollicis Brevis (APB), from which the subsequent neurophysiological assessments will be performed. The resting motor threshold (RMT), which is the minimal stimulus intensity required to evoke MEPs with amplitudes of ≥50 μV in at least five out of 10 consecutive trails, will be determined as the amplitude reference. MEP amplitude and latency, i.e., the peak to peak amplitude and the time period between stimulation onset and start of the largest MEP, will be measured and recorded. In instances where MEP will be recorded in the affected-side APB, it will be denoted as MEP (+), and if multiple measurements fail to yield a MEP, it will be denoted as MEP (−).

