#### Group-level analysis

All statistical analyses will be performed using SPSS software (SPSS 25.0, SPSS Inc., Chicago, Illinois). The intention-to-treat principle will be used for the analysis of functional and electrophysiological data. One-way analysis of variance (ANOVA) will be used to compare the demographic characteristics and baseline assessment (T0) of all outcomes among groups. To compare the treatment effects of different rTMS protocol, a two-way mixed design ANOVA with between-subject factor “Group” and within-subject factor “Time” will be performed for the clinical and electrophysiological changes. Moreover, Bonferroni correction will be employed for post hoc multiple comparisons. *P* < 0.05 will be considered statistically significant for all analyses.

For rs-fMRI and DTI data, a two-way mixed design ANOVA will be performed, with between-subject factor “Group” and within-subject factor “Time” on the data generated in the data processing step, including Eg, El, network betweenness, clustering coefficient, and FA AI. For tb-fMRI data, a whole brain paired T-test will be performed between the task state blocks and baseline blocks in the FC group, and the voxels whose t value is higher than the threshold will be regarded as the activated brain region. For cM1-LF, cPMd-HF, and CON groups, a two-way mixed design ANOVA, with between-subject factor “Group” and within-subject factor “Time” will be performed within the former activated brain region. The most significant point of “Group” × “Time” effect in the activated brain region will be used as the center to construct spherical balls with a radius of 6 mm, and the spherical balls will be regarded as the ROIs. Finally, to obtain the effective connectivity of each patient at different time points, the average time series of all voxels in each ROI will be subjected to dynamic causal model (DCM) analysis.

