#### Correlation analysis

Pearson correlation analysis will be performed between electrophysiological parameters, MRI parameters, and clinical function scores in cM1 LF group and cPMd HF group. The statistical threshold will be set to *p* < 0.05.

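### Eight clinical scales are tested at 0.05 with none ranked as primary, so error across scales is uncontrolled; FM-UL and the cPMd-HF versus cM1-LF contrast should be made primary in the analysis section

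*Protocol article*

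**What the plan says.** The section on clinical function and electrophysiological assessment of the protocol article lists the clinical outcomes, all measured at T0, T1 and T2:

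- Brunnstrom stage: "The level of motor function will be assessed based on the Brunnstrom stage".
- MMT and MAS: "Manual muscle test (MMT) and modified Ashworth scale (MAS) will be used to assess muscle strength and muscle tone of the limbs".
- NIHSS, which "will be used to assess the severity of neurological deficits in stroke".
- FM-UL, ARAT and WMFT, which "will be used to assess the motor function of the affected arm and hand".
- MBI, for activities of daily living.

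That makes eight scales. None is called primary or secondary, and no visit is given priority.

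The Group-level analysis section states that "a two-way mixed design ANOVA with between-subject factor “Group” and within-subject factor “Time” will be performed for the clinical and electrophysiological changes". It adds that "Bonferroni correction will be employed for post hoc multiple comparisons", and that P < 0.05 "will be considered statistically significant for all analyses". The Correlation analysis section repeats the level: "The statistical threshold will be set to" p < 0.05.

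Two other places signal a priority. The Abstract gives the comparison of low-frequency rTMS on cM1 with high-frequency rTMS on cPMd as the main purpose. The Sample size calculation section uses FM-UL only, from baseline to after intervention.

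**The concern.** The priorities implied by the aim and the sample size do not reach the analysis section. There, all eight scales have equal standing, each is tested at 0.05, and the only stated correction works within an outcome. Nothing says what is concluded if one scale is significant and seven are not.

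This matters because the article hypothesises that cPMd-HF may be the best protocol for these patients and expects the result to guide treatment. Under the stated rule, the scale that carries the claim can be chosen after the results are seen, and the claim then has no controlled error rate.

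**Working it through.** **The plan's own figure.** The article states no family-wise error rate. Its only design figure is 20 per group, from an FM-UL change of 43 − 30 = 13, SD 17, 80% power, 0.05 and 30% dropout. A within-group pre-post calculation with the normal formula reproduces it: ((1.96 + 0.8416) × 17/13)² = 13.4, so 14, and 14/0.70 = 20. This requires reading 17 as the SD of the change. The same inputs in a two-sided two-group comparison give 27 per group, or 39 after dropout.

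**Eight independent tests.** 1 − 0.95⁸ = 0.337, or 34%.

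**Correlated scales.** The scales overlap in what they measure, so independence is an upper case. The article gives no correlations, so a common value was assumed and varied. The simulation used 3 groups of 20, 3 visits, 8 normally distributed outcomes, no true effect, an assumed correlation of 0.7 between visits within a patient, and 3,000 runs per setting. Three events were counted:

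- A: at least one scale with a Group × Time interaction at 0.05.
- B: as A, and on the same scale some pair of groups differs in change (T0–T1 or T0–T2) at 0.05/3.
- C: as B, but the pair is cPMd-HF versus cM1-LF.

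| Assumed correlation | A | B | C |
|---|---|---|---|
| 0 | 33.5% | 25.9% | 11.5% |
| 0.5 | 26.3% | 21.0% | 10.1% |
| 0.7 | 19.4% | 15.4% | 7.1% |
| 0.8 | 17.1% | 13.5% | 6.4% |
| 0.9 | 12.3% | 9.4% | 4.3% |
| 0.95 | 9.5% | 7.6% | 3.1% |

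Simulation standard errors are below 1 percentage point, for example √(0.335 × 0.665/3000) = 0.9 points. A chi-square approximation to A with 200,000 draws gives 33.7% at correlation 0, 26.2% at 0.5 and 16.6% at 0.8; simple two-sided normal tests give 15.7% at 0.8.

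**After the fix.** One pre-named test at 0.05 has a 5% false-positive rate. For comparison, Bonferroni over eight scales uses 0.05/8 = 0.00625 each, and 1 − (1 − 0.00625)⁸ = 4.9% if independent.

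**Power for the head-to-head contrast**, if the true difference between arms were 13 with SD 17:

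- 20 per group: standard error 17 × √(2/20) = 5.38; 13/5.38 − 1.96 = 0.46; power 68% (65% with the t distribution).
- 14 completers per group: standard error 17 × √(2/14) = 6.43; 13/6.43 − 1.96 = 0.06; power 53% (50% with the t distribution).

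**The case against.** The strongest reply is that the article does show its priorities: the main purpose names one contrast and the sample size names one outcome. A reader might infer that nothing is singled out anywhere, and that would be wrong. What stands is narrower: neither priority is carried into the analysis section, and a planning variable is not a decision rule.

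A second reply concerns size. A reader might take 16–34% as the chance of falsely declaring one protocol better. The documents do not support that. An interaction alone names no better arm, and a Bonferroni-corrected comparison stands between it and any such claim. The figures for such a claim are those under B and C. By symmetry only about half of C would favour cPMd-HF, and at a correlation of 0.9 or more C falls below 5%.

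Third, a reader might infer that any visit or contrast reaching 0.05 would do. That overlooks the single mixed ANOVA, which takes the visits together, and the post hoc correction. The gap that clearly remains is across scales.

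Fourth, the count of eight can be disputed. Counting only Brunnstrom, FM-UL, ARAT and WMFT as motor function gives 1 − 0.95⁴ = 18.5% for A under independence. That is smaller, but still well above 5%.

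Fifth, the analysis plan is not shown, and detailed multiplicity control for secondary and imaging outcomes is commonly left to it. That is accepted, and nothing here rests on it. A reader might also multiply the 90 network nodes into 90 betweenness tests, but the article does not say that each node is tested. The correlations within the active arms cannot yield a claim that one arm is better. What is at issue is a rule the article itself states for every analysis, together with an unranked outcome list; ranking the outcomes is a protocol decision.

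**Conclusion.** The point holds in this form: eight unranked scales, a blanket 0.05 and no control across scales leave a superiority claim free to rest on whichever scale is significant. Over assumed between-scale correlations of 0 to 0.8, the error is about 34% to 16% for any false interaction, about 26% to 13% for any false pairwise claim, and about 12% to 6% for cPMd-HF versus cM1-LF. These figures count one score per scale, assume no true effect and normally distributed data, and depend on correlations that the article does not give. Stronger correlation lowers them; adding electrophysiological outcomes or subscores would raise them. For the contrast the trial is mainly about, the inflation is moderate rather than extreme.

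**What to change.** In the Group-level analysis section, before unblinding:

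1. Name FM-UL change from T0 to T1 as the single primary outcome, with cPMd-HF versus cM1-LF as the primary contrast at two-sided 0.05.
2. Then test each active arm versus sham on FM-UL in a stated fixed order, each at 0.05 only if the test before it is significant.
3. Label the other scales, T2, electrophysiology, imaging and the analyses in the Correlation analysis section as secondary or exploratory.
4. Limit the sentence that applies P < 0.05 to all analyses to the ordered tests in 1 and 2.
5. Restate the power for the primary contrast in the Sample size calculation section.

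The first four are changes of wording and use priorities the article already signals; their cost is that secondary results lose confirmatory status. The fifth is a real cost. The 13 points are a change within low-frequency rTMS patients, not a difference between arms. Even taking 13 as the difference with SD 17, power is about 65–68% at 20 per group and about 50–53% with 14 completers, so the stated 80% cannot be kept for this contrast without different assumptions or more patients.

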### Randomization and grouping

The 60 eligible stroke patients will be randomly assigned to three groups with 20 patients in each group: low-frequency rTMS of cM1 (cM1-LF) group, high-frequency rTMS of cPMd (cPMd-HF) group, and sham-stimulation control (CON) group. The random sequence will be created using STATA 12.0 software (StataCorp, Texas, USA) by a professional third-party statistician from Fudan University. The randomization list will only be known by this research coordinator and will be concealed from other study personnel. However, the research coordinator will not participate in recruitment, subsequent intervention and assessment, and final data analysis. In addition, 20 healthy people will be recruited into the healthy control (HC) group. The HC group will be matched with stroke groups in terms of age, gender, and education.

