### Data processing and analysis

#### MRI preprocessing

MRI data will be preprocessed using SPM 8 software. The data of patients with left hemisphere lesions will be flipped along the midsagittal plane to ensure that all the patients have “virtual” right hemisphere lesions. SPM 8 will also be used for BLOD fMRI data preprocessing. Slicing timing, realignment, normalization, and smoothing will be performed on the BLOD fMRI data. Next, the data with translation parameter greater than ±2.5 mm or rotation parameter greater than ±2.5 degrees will be removed. Finally, the diffusion toolkit software (http://www.trackvis.org/dtk/) will be used to pre-process the DTI data.

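### P < 0.05 is set for all analyses and no correction is named for the voxels searched in the task-fMRI Group × Time test; read literally, the chance of a false activation difference is far above 5%

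*Protocol article*

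**What the plan says.** All of this is in the protocol article, mostly in Statistical analysis, Group-level analysis.

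- **Level.** The first paragraph ends by stating that P < 0.05 "will be considered statistically significant for all analyses".
- **Correction.** Just before that, after the ANOVA for clinical and electrophysiological outcomes, it says "Bonferroni correction will be employed for post hoc multiple comparisons". No family-wise, false-discovery-rate, cluster or small-volume correction is named anywhere in the article.
- **Search region.** The second paragraph starts from a whole-brain t-test in one group (labelled FC, apparently the healthy controls): "the voxels whose t value is higher than the threshold will be regarded as the activated brain region". The value of that threshold is not given, and it applies to the t map only.
- **Arm comparison.** For the three patient groups, a mixed ANOVA of Group by Time "will be performed within the former activated brain region".
- **Use of the result.** "The most significant point of “Group” × “Time” effect in the activated brain region will be used as the center" of 6-mm spheres, which then supply the time series for dynamic causal modelling.
- **Software.** The same section assigns all statistical analyses to SPSS 25. MRI preprocessing names SPM 8, for preprocessing only.

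**The concern.** A most significant point inside a region exists only if the test was run at many points, so the Group × Time ANOVA is a voxelwise search. A level of 0.05 at each voxel controls the error at that voxel, not over the region. Post hoc Bonferroni deals with pairs of groups or visits after an interaction has been found; it does nothing about the number of voxels at which the interaction was tested.

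At stake is how an arm-by-time activation finding is read. The Discussion presents task fMRI, with the other modalities, as a way to understand the neural effects of the different rTMS regimens. If the written rule is followed, some voxels would usually pass even when the regimens have identical effects on activation, and a reader could take them as evidence of different reorganisation.

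**Working it through.** **Inputs from the article.** Patients are "randomly assigned to three groups with 20 patients in each group" and are scanned at T0, T1 and T2. The level is 0.05. For the BOLD data, "Slicing timing, realignment, normalization, and smoothing will be performed", but no kernel is given.

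**Assumptions.** Voxels of 3 mm (27 mm³), smoothness of 6, 8 or 10 mm FWHM, and a compact cubic search region of 1.7 to 59 cm³. Table 3 gives a 5-mm slice thickness for task fMRI, but the article gives no in-plane or resampled voxel size, smoothing kernel or region volume.

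**Degrees of freedom.** Interaction: (3 − 1) × (3 − 1) = 4. Error: (60 − 3) × (3 − 1) = 114.

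**The plan's own figure.** The article states no error rate for the voxel search, only the nominal 0.05. In a simulation with no true effect, the share of voxels with P < 0.05 was 0.046 to 0.061 across settings. The simulated test therefore behaves as intended at the single voxel.

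**Simple check.** For m independent tests at 0.05, the chance of at least one false positive is 1 − 0.95^m:

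- m = 10: 0.40
- m = 20: 0.64
- m = 45: 0.90
- m = 59: 0.95
- m = 100: 0.994

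Neighbouring voxels are correlated, so m is not the voxel count. The smooth-field simulation allows for this.

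**Simulation.** Smooth Gaussian noise, 20 per arm, F with 4 and 114 df at each voxel, 200 runs per setting. Chance that at least one voxel has P < 0.05 with no arm difference:

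| Region | Voxels | FWHM 6 mm | FWHM 8 mm | FWHM 10 mm |
|---|---|---|---|---|
| 1.7 cm³ | 64 | 0.81 | 0.63 | 0.50 |
| 9.3 cm³ | 343 | 1.00 | 0.975 | 0.95 |
| 27.0 cm³ | 1000 | 1.00 | 1.00 | 0.995 |
| 59.3 cm³ | 2197 | 1.00 | 1.00 | 1.00 |

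The simulation standard error is √(0.95 × 0.05/200) = 0.015 at 0.95 and √(0.5 × 0.5/200) = 0.035 at 0.50.

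A separate simulation with 14 completers per arm (20 × 0.7, the article's 30% dropout), F with 4 and 78 df, 60 runs per setting and regions of 9 to 79 cm³ gave 0.97 to 1.00.

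**How a null peak would look.** The median P at the strongest null voxel was 0.003 to 0.008 at 9.3 cm³ and 0.0003 to 0.001 at 59.3 cm³.

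**What a 5% error would need.** The 5th percentile of the null peak P was about 0.000025 to 0.00027 over the regions of 9 to 59 cm³ (approximate, with 200 runs). The uncorrected P at the peak would have to fall below a value in that range, depending on volume and smoothness.

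**The case against.** The best case on the other side has four parts.

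1. **Scope of the 0.05 sentence.** It closes the paragraph on clinical and electrophysiological data, and imaging starts in the next one. The Correlation analysis section states its own 0.05, which would be redundant if the earlier sentence governed everything. A level of 0.05 could also refer to a corrected P value, and a journal article need not print every imaging threshold. This is arguable, but the sentence says all analyses, with no limit to its paragraph, and the only correction named is of another kind. As printed, it is a rule that gives the wrong error rate and not just a detail left out.

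2. **Stated use of the map.** The only use given for the Group × Time map is to place spheres for the connectivity model. The Aims and hypotheses section speaks of structural, functional and effective connectivity, not activation. This stands as a limit on importance: the activation comparison is secondary.

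3. **Dependence on assumptions.** Volume, voxel size and smoothness are all assumed. This stands. A small region or smoother data lower the figure, although the lowest value in the table, 0.50, is still ten times 0.05. A whole-brain activation map of passive hand movement is unlikely to cover only 2 cm³, but the article does not settle that.

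4. **Software.** A correction in SPM is not free of consequences when the article assigns all statistical analyses to SPSS. This stands and belongs in the fix.

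A reader might also infer that the activation comparison cannot come out negative, or that any reported activation difference would carry no evidence at all. The document does not support this. Only the peak-selection step always returns a result, and that step places a region of interest; it does not declare an effect. The significance test itself can be negative, in up to about 5% of null data sets at 9 cm³ and more often in smaller regions. A peak well beyond the range needed for a 5% error would still be informative.

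**Conclusion.** The concern holds in a limited form. As printed, the blanket 0.05 covers the voxelwise task-fMRI Group × Time test, and nothing named in the article corrects for the voxels searched. The resulting chance of at least one false voxel is about 95–100% for regions of 9 cm³ or more and 50–81% at about 2 cm³. This rests on 3-mm voxels, 6–10 mm smoothness and Gaussian noise. The exact size is conditional on those inputs; that it far exceeds 5% held in every setting tried. The selected peak alone does not show that the arms differ. The point should be corrected before the imaging analysis, but it touches a secondary mechanistic result and leaves the comparison of clinical outcomes unaffected.

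**What to change.** In Group-level analysis:

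- Exempt the voxelwise task-fMRI test from the general 0.05 rule. Declare a Group × Time activation effect only at family-wise-error-corrected P < 0.05, at peak or cluster level, over the search region.
- Add that if nothing survives, the report will say that no activation difference between arms was shown, and that the location of the largest F value will not be presented as an effect.
- State that the voxelwise analysis is run in SPM, and limit the SPSS sentence to the other analyses.

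The cost is a few sentences, fixed before the group codes are broken. No new data are needed, and SPM gives corrected P values from the same model. The downside is that fewer activation differences will be called significant.

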Currently, only sporadic reports of high frequency rTMS on cPMd in stroke treatment exist. Johansen-Berg et al. [31] stimulated the cPMd of stroke patients with mono-pulse TMS, and found a negative correlation between the stimulus intensity and the lateral index of PMd activation in task-based fMRI, as well as a positive correlation to the hemiplegic hand motor function score. This suggests that TMS is capable of activating excitatory effects on cPMd, and facilitating the motor recovery of upper limb and hand in stroke patients. In addition, Bestmann et al. [32] found that stroke patients with more severe dysfunction demonstrated more activation in cPMd and the posterior part of M1 (BA4p) on the affected side when a single high-frequency TMS stimulated cPMd. This suggests that exciting cPMd with single high-frequency TMS may cause the activation points of the affected hand projection cortex to shift backward, thereby promoting functional recovery. A recent randomized sham-controlled crossover study published in 2017 compared the effects of single-pulse low-frequency TMS on M1, high-frequency TMS on cPMd, and sham stimulation in 15 stroke patients. The results showed that treatment using single-pulse high-frequency TMS on cPMd resulted in a greater improvement than using single-pulse low-frequency TMS on cM1 in severely affected patients [33]. However, these evidences were all based on cross-sectional studies, and longitudinal treatment studies on single-pulse high-frequency rTMS of cPMd are still lacking. Moreover, most of the existing studies utilized single-mode fMRI analysis, which could not thoroughly demonstrate the brain network reorganization patterns of rTMS in promoting functional recovery in stroke patients. Therefore, future studies should use multimodal fMRI (structural, functional, and effective network) to elucidate the mechanisms of this new protocol of rTMS in stroke rehabilitation from multiple perspectives of neural repair and remodeling.

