### Aims and hypotheses

This study will conduct a longitudinal, single-blinded, randomized controlled trial to verify the clinical effects of different protocols of rTMS therapy on functional recovery of chronic subcortical stroke patients with severe hemiplegic upper limb. To the best of our knowledge, this is the first study to compare the effects of low-frequency rTMS on cM1 and high-frequency rTMS on cPMd. We expect that the findings will provide vital information about the optimal rTMS strategy. Multimodal fMRI scanning and electrophysiological measurements will be performed longitudinally to elucidate the underlying neural mechanism of brain reorganization after different parameters of rTMS therapy. We hypothesize that high-frequency rTMS on cPMd might be the optimal protocol for motor functional recovery in chronic subcortical stroke patients with severe hemiplegia. This clinical effect may be attributed to the specific remodeling patterns of structural, functional, or effective connectivity of homologous or allogeneic cortexes within or between hemispheres through multimodal neural imaging analysis. Furthermore, joint analysis of the clinical and neuroimaging results might identify the cut-off of structural reserve that determines the application of high/low frequency rTMS on contralesional hemisphere to achieve maximum functional recovery of the paretic upper limb.

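### DCM regions are centred on the Group × Time peak of the same patients' task fMRI, so any later arm-by-time comparison of effective connectivity is non-independent and may not involve cPMd

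*Protocol article*

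**What the plan says.** The task-fMRI steps are in the Group-level analysis section of the protocol article:

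1. **Mask.** For task fMRI, "a whole brain paired T-test will be performed between the task state blocks and baseline blocks in the FC group", and voxels above a threshold count as activated. FC is not defined as a group. The three patient arms are listed separately in the next sentence, so the healthy control (HC) group appears to be meant.
2. **Search.** A Group × Time mixed ANOVA of the three patient arms "will be performed within the former activated brain region".
3. **Regions.** The peak of the Group × Time interaction "effect in the activated brain region will be used as the center to construct spherical balls with a radius of 6 mm".
4. **DCM.** The stated purpose of the last step is "to obtain the effective connectivity of each patient at different time points". To that end, "the average time series of all voxels in each ROI will be subjected to dynamic causal model (DCM) analysis".

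No separate run, hold-out sample or leave-one-out step is named between steps 2 and 4. The Aims and hypotheses section says that the clinical effect may be due to "specific remodeling patterns of structural, functional, or effective connectivity of homologous or allogeneic cortexes within or between hemispheres". The Background names cPMd as the region of interest.

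**The concern.** It is common to place DCM nodes at activation peaks. Here the peak is that of the between-arm change over time, which is the contrast the trial is about, and it is found in the scans that then supply the DCM time series. The chosen location is the one where chance and true effect together most favour an arm difference. If coupling estimates share any variation with activation there, a later arm-by-time comparison inherits the advantage, and its nominal 5% level no longer holds.

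The second risk concerns the question itself. The mechanistic hypothesis is about cPMd compared with cM1, but the data decide where the nodes fall. A DCM without a cPMd node cannot say anything about cPMd coupling.

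**Working it through.** The plan gives no error rate for this step, so there is no figure to reproduce. The effect was checked by simulation.

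**Inputs from the protocol article:** 3 arms of 20 (Randomization and grouping); 3 visits, T0, T1 and T2 (fMRI scan); significance level 0.05 (Group-level analysis); 30% dropout (Sample size calculation), leaving 20 × 0.7 = 14 per arm.

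**Assumptions, not in the article:** R, the number of independent regions in the mask (20, 100, 300); ρ, the correlation between activation at the selected peak and the connectivity measure (0 to 1).

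**Model under no effect:** activation A is standard normal for each patient, visit and region. For each region, F = [SS(Group × Time)/4] / [SS(error)/(2 × 3 × (n − 1))], so the error df are 114 for n = 20. The region with the largest F is selected. Connectivity is C = ρ·A(peak) + √(1 − ρ²)·e, with e independent standard normal, and is tested for Group × Time at 0.05. There were 2,000 runs per setting.

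Type I error of the connectivity test:

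| n per arm | R | ρ = 0 | ρ = 0.3 | ρ = 0.5 | ρ = 0.7 | ρ = 1 |
|---|---|---|---|---|---|---|
| 20 | 20 | 4.4% | 7.1% | 12.2% | 23.4% | 64.7% |
| 20 | 100 | 4.0% | 9.4% | 20.4% | 41.8% | 99.6% |
| 20 | 300 | 4.8% | 11.2% | 26.4% | 52.3% | 100% |
| 14 | 100 | 5.1% | 10.8% | 22.0% | 41.8% | 99.4% |

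The simulation standard error is √(0.204 × 0.796/2000) = 0.9 percentage points at 20.4%, and 1.1 at 41.8%. A repeat of the n = 20, R = 100 case gave about 10%, 20% and 41% at ρ = 0.3, 0.5 and 0.7, which agrees.

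**Region fixed in advance:** 4.0% to 5.8% for every ρ, R and n tried.

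**Does the peak fall on cPMd?** Suppose cPMd is inside the mask and is the only region with a true effect, a shift in one arm at T1 and T2 (n = 20, 1,000 runs per setting). The peak lands there in:

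| Shift (within-subject SD) | R = 20 | R = 100 | R = 300 |
|---|---|---|---|
| 0.4 | 12.3% | 3.4% | 1.5% |
| 0.7 | 27.6% | 13.3% | 6.9% |
| 1.0 | 54.4% | 33.6% | 20.8% |

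If cPMd is outside the mask, it cannot be chosen. The article also speaks of one most significant point but of several spheres, so how further nodes are found is unclear.

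**The case against.** **The arm test is not written.** The section stops once connectivity has been obtained for each patient and visit. The Correlation analysis section speaks of MRI parameters without saying whether DCM parameters are among them. This stands: the comparison is implied by the section heading, the per-visit estimates and the hypothesis, but not stated.

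**The size depends on ρ.** Activation and coupling are different quantities, and at ρ = 0 there is no inflation. This also stands. Exactly zero is hard to defend, though, because DCM is fitted to the selected time series.

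**A significance gate may apply.** The article sets P < 0.05 for all analyses, so spheres might be built only when the interaction is significant. The text does not say so. At an uncorrected 0.05 it would protect little: with 100 independent null regions, the chance that at least one passes is 1 − 0.95^100 = 99.4%. That figure measures search multiplicity and is not the bias in connectivity, though a reader might take it as such.

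**Stronger readings that the article does not support:**

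- *Arm differences in task activity are biased too.* The only planned arm comparison of activity is the ANOVA within the mask. The mask appears to come from other people and is then not circular, and no second test of activity in the spheres is planned.
- *The mask excludes cPMd.* The Background reports that "stroke patients with more severe dysfunction demonstrated more activation in cPMd", but that sentence describes activation while TMS was applied to cPMd. It does not show that cPMd is silent in healthy people during this task. For the paretic hand, cPMd lies ipsilateral to a passive movement, so activation is not assured. But both hands are tested and the threshold is not given. Exclusion is only possible.
- *The whole mechanistic aim fails.* The resting-state network measures and FA asymmetry do not use these spheres.

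**Conclusion.** The selection rule is stated in full and is unsound for its purpose. As written, any later arm-by-time reading of the DCM parameters is non-independent. Under the null, with 20 per arm and 100 independent regions, type I error is about 10%, 20% and 41% at correlations of 0.3, 0.5 and 0.7, against about 5% for regions fixed in advance. Both the number of regions and the correlation are assumptions. The direction is secure for any non-zero correlation, but the size is not known.

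Separately, nothing ensures a node at cM1 or cPMd, and the mask may leave cPMd out, so the effective-connectivity part of the cPMd hypothesis may go untested. The resting-state, DTI and clinical analyses are unaffected. The change should be made, but it does not touch the clinical comparison.

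**What to change.** - Name the DCM nodes in advance: bilateral M1 and PMd, with SMA optional.
- Centre each 6-mm sphere on an anatomical definition, or on the task-versus-rest peak pooled over all arms at T0 and the controls. The pooled choice does not depend on Group × Time: with a common variance, the mean over all patients has the same covariance with each arm's mean, so its covariance with any difference between arms is zero.
- Do not use the TMS stimulation site as the centre unless its registration to MRI is described. The intervention section gives only an offset from the M1 hotspot.
- Use as mask the union of healthy-control activation and pooled-T0 patient activation, and correct FC to the intended group.
- Keep the Group × Time map as a separate, multiplicity-corrected exploratory analysis that does not define DCM nodes.

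The cost is imaging-analysis wording, with no new scans. Preset nodes may miss an unexpected region, but the exploratory map still covers that.
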